**Research Question 2b**: Do measures of user preferences identified during a brief test-drive session with an *actual* AFO predict user preferences after the same *actual* AFO is worn longer-term in the community environment?

**Hypothesis 2b**: Initial preference scores for each *actual* AFO be strongly correlated with preference at follow-up.

**Research Question 2c**: Do measures of user preferences identified during a brief test-drive session correlate with performance measures and self-reported measures of mobility after the same *actual* AFO is worn longer-term in the community environment?

**Hypothesis 2c**: Initial *emulated* preference scores be strongly correlated with performance-based and self-reported mobility measures at follow-up.

**Research Question 2d**: Do measures of user preferences identified during a trial with the *actual* AFO correlate with performance measures and self-reported measures of mobility after the same AFO is worn longer-term in the community environment?

**Hypothesis 2d**: Initial *a*ctual preference scores be strongly correlated with performance-based and self-reported mobility measures at follow-up.

**Exploratory Aim:** Allow the user to self-tune AFO emulator stiffness settings while walking (***patient-optimized***) and compare function, mobility, preference to the clinically prescribed AFO (***clinician-optimized***). This aim will determine if an AFO test drive strategy can be used to better optimize user satisfaction and patient reported outcomes relative to the current standard of care.

**Research Question 3a**: How does preference differ between the patient-optimized setting on the AFO emulator and in the clinically-prescribed *actual* AFO?

**Hypothesis 3a**: Preference scores for the user-optimized setting on the emulator will be greater than those in the clinically prescribed AFO.

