# Study Procedures

## 4.1 Study Design

This is a clinical trial with a participant-blinded, cross-over study design with repeated-measures assessments will take place at each site. Short-term, in-lab sessions will be used to address Aim 1 (i.e., comparing in-lab *emulator* trials to in-lab corresponding *actual* AFO trials) and the Exploratory Aim (comparing in-lab patient-optimized emulator trials to in-lab prescribed *actual* AFO trials). Aim 2 will compare short-term in-lab trials with longer-term follow-up using corresponding *actual* AFOs. We will assess user preference, satisfaction, perceived mobility and performance in *emulated* and *actual* AFOs to determine whether the emulator and/or a brief trial of *actual* AFOs can predict user mobility and AFO preference following longer term use in the community environment.

See section 5.5 below for data collection procedures.

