**Actual AFO testing session.** Prior to the start of the testing session, participants will be fit with the three actual AFOs to be worn during the data collection. Fitting will be done according to the routine standard of clinical care (e.g. test device for the custom AFOs). On the day participants complete the actual AFO testing, they will walk on the treadmill in each AFO condition to acclimate prior to testing. Then, participants will undergo the same Activities Trial as in the emulated AFO testing session (described below). The same questionnaires will be completed to identify patient-reported outcomes. In the actual AFO testing session, participants will additionally complete a series of performance tests described below.

**Two-week follow up sessions**. Participants will complete two-week long community trials in each of the three actual AFO conditions in a randomized. AFOs will have already been fit to each subject as described above. Participants will be instructed to wear the study AFO instead of their clinically-prescribed AFO for all usual activities of daily living. After two weeks of wearing each AFO, participants will return to the laboratory for follow-up evaluation; Patient-Reported Outcomes and Performance Tests will be assessed. A subset of participants may also have the activities trial collected and/or gait biomechanics collected at the two-week follow up sessions.

**The Exploratory Session** will compare a participant’s clinically prescribed AFO (clinician optimized) to a participant-optimized setting on the emulator. Stiffness will be the optimized parameter. In this exploration, participants will be allowed to dial in and change the stiffness parameters on the emulator so that they self-identify an optimal value (patient-optimized).

**Figure 1.** Study Overview

**
[figure not shown]
**

**Activities Trial**. The activities selected are intended to represent a range of activities commonly encountered in the community environment (Table 1). As detailed below, activities will be assigned in a manner specific and appropriate to the individual patient (e.g., participants of a lower mobility or with contraindications will not be asked to run). Each speed and activity condition will take place for at least 30-seconds and rest will be provided between activities as needed. After each AFO condition is complete, participants will rest for at least 10 minutes before engaging in the next AFO condition.

| **Activities Trial** |
| --- |

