**Hypothesis 2B**. In Specific Aim 2B, we are testing the hypothesis that the experimental AFO preference measured during the in-lab *actual* AFO session will be significantly correlated with the experimental AFO preference measured during the take home-trials. This model operates the same as in 1A, substituting measures of take-home trial preference as the dependent variable.

**Hypothesis 2C**. In Specific Aim 2C, we are testing the hypothesis that measures of preference will be significantly correlated between the *emulated* in-lab session and measures of performance and self-reported measures of mobility at the take-home trials. This model operates the same as in 2A, substituting measures of performance and self-reported outcomes for preference as the dependent variable.

**Hypothesis 2D**. In Specific Aim 2D, we are testing the hypothesis that measures of preference will be significantly correlated between the *actual* in-lab session and measures of performance and self-reported measures of mobility at the take-home trials. This model operates the same as in 2A, substituting measures of performance and self-reported outcomes for preference as the dependent variable.

**Power Analysis for Aims 1 & 2**. Our power analysis is based upon pilot data collected for a similar study using prosthetic feet which tested mobility and preference for three participants and two feet between *emulated* and *actual* sessions. Based upon the estimates of slope and residual error from the pilot data, 10,000 datasets were created for a sample size of N=50. Power, estimated as the proportion of datasets that rejected the null hypothesis of a slope equal to zero, was 97% for the preference scores and 98% for the mobility scores. To account for a 12% dropout rate (note that prior prosthetic emulator study experienced a 7% dropout rate) a total sample of N=56 participants will be tested.

**Exploratory Aim**. In this exploration, participants will be allowed to dynamically “dial-in” and change in the stiffness settings of the emulator device so that they design an optimal device to meet their needs. The *emulated* device will then be compared to the device that was clinically prescribed for them as part of usual care. To test the hypothesis a simple paired t-test will be used which compares the preference means and other outcomes measures of the patient-optimized and clinician-optimized conditions.

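### The exploratory t-test compares a self-tuned emulator with the participant's own brace, so it cannot support the stated conclusion about standard of care

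*Protocol*

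**What the plan says.** Protocol 4.5 (The Exploratory Session) defines the patient-optimized condition: "participants will be allowed to dial in and change the stiffness parameters on the emulator so that they self-identify an optimal value". It adds: "Stiffness will be the optimized parameter".

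Protocol 4.6 (Exploratory Aim) names the comparator. The emulated "device will then be compared to the device that was clinically prescribed for them as part of usual care". It also names the analysis: "To test the hypothesis a simple paired t-test will be used which compares the preference means and other outcomes measures". Section 4.1 confirms the pairing as the patient-optimized emulator against the prescribed actual AFO, both in the lab.

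The Objectives give Hypothesis 3a: "Preference scores for the user-optimized setting on the emulator will be greater than those in the clinically prescribed AFO". They also give the aim's wider purpose: "This aim will determine if an AFO test drive strategy can be used to better optimize user satisfaction and patient reported outcomes", measured against the current standard of care.

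Section 4.1 describes the study as having a "participant-blinded, cross-over study design".

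**The concern.** Stiffness is the one parameter the participant tunes, but it is not the only thing that differs between the two conditions. One is a tethered, externally actuated exoskeleton with a worn mass of 1.4 kg including the shoe (Introduction, Test-drive strategies). The other is the brace the participant already uses. The participant has also just chosen one of the two settings and then rates both on a subjective 10-point scale.

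A result in either direction could therefore come from the platform, or from the expectation that follows having just chosen, with no benefit or harm from tuning. If the result is read as the Objectives invite, the trial could report that a test-drive strategy beats standard prescription, or fails to, on evidence that does not separate the two explanations. The participant-blinded label in 4.1 may add false reassurance, since someone who dials in a setting and then rates it against their own brace is not blind to which is which.

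**Working it through.** **1. What differs between the two conditions**

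| Feature | Patient-optimized | Clinician-optimized | Source |
|---|---|---|---|
| Platform | Emulator | Own physical AFO | 4.1, 4.5, 4.6 |
| Stiffness chosen by | Participant, in session | Clinician, beforehand | 4.5, 4.6 |
| Identity known to participant | Yes | Yes | follows from 4.5 |

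Each condition has one platform and one chooser, so the two factors are completely aliased. The emulated conditions in 4.5 correspond to the three study AFOs. No emulation of the prescribed AFO is described, and no physical AFO is made at the self-tuned stiffness.

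**2. What the t-test estimates**

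For participant i, let D_i be the emulator score minus the prescribed-AFO score. Then

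E(D) = tuning effect + platform offset + effect of having just chosen.

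The paired t-test estimates the sum. An offset of c points moves the estimate by exactly c.

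**3. Whether Aim 1 would reveal the offset**

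Aim 1 (4.6) regresses the actual score on the emulated score with a random intercept and tests the slope:

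actual = a + b × emulated + u + e.

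If every emulated score is shifted by c, the fit becomes actual = (a − bc) + b × (emulated + c) + u + e. The slope b is unchanged and only the intercept absorbs the shift. In a simulated data set (50 participants, three devices), the fitted slope was 0.754 with shifts of 0, −2 and +2 points. A significant Aim 1 slope is therefore compatible with a large mean gap between emulated and actual scores.

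**4. How much an offset could matter (illustration)**

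The power statement in 4.6 covers Aims 1 and 2 only, so there is no plan figure to reproduce here. The protocol gives no SD, offset, sample size, alpha or sidedness for this test. Assumptions: tuning effect zero, two-sided alpha 0.05, SD of paired differences 2.5 points, n = 30 or 50.

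- Standardised offset: d = c / SD. For c = 1, d = 1/2.5 = 0.4; for c = 0.5, d = 0.5/2.5 = 0.2.
- Noncentrality: d × √n. For d = 0.4 this is 2.19 (n=30) and 2.83 (n=50). For d = 0.2 it is 1.10 and 1.41.
- Critical t: 2.045 (29 df) and 2.010 (49 df).

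Probability of a significant result in the direction of the offset, from the noncentral t distribution:

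| Offset | SD | n=30 | n=50 |
|---|---|---|---|
| 0 | any | 2.5% | 2.5% |
| 0.5 point | 2.5 | 18% | 28% |
| 1 point | 2.5 | 56% | 79% |
| 1 point | 2.0 | 75% | 93% |
| 1 point | 3.5 | 33% | 51% |

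An offset against the emulator would hide a real tuning benefit in the same way.

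**The case against.** The best defence is that the t-test answers the question asked. Research Question 3a and Hypothesis 3a name both platforms: the self-tuned emulator setting and the prescribed actual AFO. Section 4.6 compares exactly those two. Nothing in the protocol says that the whole difference is due to stiffness. This stands: the test is a valid estimate of a package difference, and a reader who infers that Hypothesis 3a is untestable or the t-test invalid goes too far.

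Several further points also stand:

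- Self-choice is largely the intervention. Patient input is the strategy under study, so only the expectancy from having just chosen is a nuisance.
- Novelty is a weak explanation. The emulated session in 4.5 includes an accommodation period and three emulated conditions.
- A reader might infer that the prescribed AFO has lain unused for the three community periods by visit 7. The document does not say what is worn between periods or before that visit.
- The session is openly described as optional, and a condition order not spelled out in an exploratory paragraph is operational detail. Neither is an error.
- A reader might infer that only the emulator setting can be masked and that every actual-AFO phase is open-label. The document does not show this. Participants can see a brace without being told its model or stiffness class, and the Privacy and Confidentiality section codes devices as 1, 2 or 3. The label clearly fails only for the exploratory comparison.
- A false-positive rate near 80% is one cell of the table. It needs n=50 at an optional visit, an assumed SD and an assumed offset favouring the emulator.

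The defence does not rescue the purpose statement. The Objectives go beyond Research Question 3a and say the aim will settle whether a test drive can be "used to better optimize user satisfaction and patient reported outcomes relative to the current standard of care". A package contrast on a tethered laboratory device cannot settle that, even if the plan is carried out exactly.

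**Conclusion.** The point holds as a mismatch between the contrast and the conclusion drawn from it. The exploratory t-test estimates platform plus self-tuning together, including expectancy, and Aim 1's slope gives no protection against a mean offset. The supported conclusion is about in-lab preference for the self-tuned emulator over the prescribed AFO, and no wider.

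The algebra in steps 2 and 3 needs no assumed figures. The size does: the probabilities in step 4 depend on an assumed SD, offset and number attending, and the direction of any offset is unknown. They show that a moderate offset would matter, not that one exists.

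Severity is minor. The aim is labelled exploratory, the session is optional, and no Aim 1 or Aim 2 hypothesis is affected.

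**What to change.** 1. **Objectives, Exploratory Aim.** Limit the conclusion to in-lab preference, and the other outcomes measured in that session, for the self-tuned emulator compared with the prescribed AFO. Drop the inference about standard of care. Cost: rewording only.

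2. **4.6, Exploratory Aim.** Keep the planned t-test and add a sensitivity analysis. For each participant, compute O_i, the mean in-lab emulated-minus-actual difference over the three study AFOs, and analyse D_i − O_i. State that this assumes the offset carries over from the study AFOs to the prescribed AFO, and that it does not remove familiarity or self-choice. Cost: one more analysis of data that Aim 1 already collects.

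3. **4.1.** Limit the participant-blinded description to the phases where device or setting identity is actually withheld, and state that the exploratory comparison is not blinded. Cost: one sentence.

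Optional only: add an emulated condition at the prescribed AFO's measured stiffness, with the setting undisclosed and the order randomised. This would hold the platform constant. It needs an extra condition and a bench measurement, and it answers a different question, because the prescribed device itself drops out of the contrast. It should not replace the planned comparison.

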## 4.7 Withdrawal of Subjects

A study clinician or PI may withdraw a participant without their consent if he or she feels that it is not in a participant’s best interest to continue in the study or the person is unable to complete the study procedures. All data previously collected from participants who withdraw or are withdrawn will be kept and may be used in the study data analysis. Participants may withdraw at any time by informing the Research Coordinator and/or the PI.

# Reporting

All safety information on AEs, SAEs, unanticipated events or problems, and protocol deviations will be collected. This information will be collected at study visits and whenever subjects call to report a problem. The information will be collected on VA IRB forms (Report of a SAE and/or Problem Form, or Report of Problems (ROP) Form) and in AE log forms as needed. Safety data will be collected on an as-needed basis and will begin upon enrollment into the study. All safety reporting requirements will be followed. Any anticipated AEs will be recorded on a log sheet and reported annually with the CRQ.

Unanticipated SAEs, protocol deviations and/or serious problems that are related to the

research will be reported to the Central IRB within 5 business days of becoming aware of the event. After each report of a U-SAE or problem, and/or SAE, the Medical Monitor will evaluate study procedures for previously assessed risks, and will determine whether any changes must be made to minimize risks. The Medical Monitor has the authority to stop the research protocol in progress, remove individual participants from the research protocol, and take whatever steps are necessary to protect the safety and well-being of human subjects until the IRB assesses SAEs or other reports. Reports for events determined by either the investigator or Medical Monitor to be possibly or definitely related to participation and reports of events resulting in death will be promptly forwarded to the USAMRMC ORP HRPO. Cumulative safety data will be reviewed yearly by the Site PIs and the Medical Monitor, and will be reported to the VA and DoD IRBs during continuing reviews. The above procedures are standard practice at VAPSHCS and WRNMMC and we will involve a Medical Monitors with whom we have worked previously in this capacity.

# Privacy and Confidentiality

As with any study, it is possible, although unlikely given the impersonal nature of the data collected, that participants may experience a loss or invasion of privacy or confidentiality because of participation in this study. The risk of harm is minimal and the protections described here will be followed.

Participant data will be collected the study sites and will be entered into independent and secure databases. In general, electronic data will be coded with links stored separately, stored on password protected drives, servers will be backed up regularly, firewalls in place, and access permitted only by study team members listed on the approved IRB protocol. Hard copies of data forms will contain only codes and be stored in locked cabinets (dedicated to this study’s records), and locked offices with access only given to study team members. Informed consent documents will be stored separately along with other identifiable information (such as records necessary to have in paper form, which will be limited). Because this is a multi-site study, extra care will be taken not to share PHI or other identifiable information about participants across centers.

To protect privacy and confidentiality during data collections, all data collected will have PHI removed and participants will be issued an alpha-numeric code which will be used to track their records. Subject records will be coded with a unique identifier. The first five characters will be an abbreviation of the study (AFO Test Drive - AFOTD) to identify to which study the subject belongs followed by a site identifier (WR = Walter Reed, VA = VAPSHCS) and sequential numbering based on the subject order of enrollment. The device tested will be indicated as device 1, 2, or 3.

# Communication Plan

All human subjects data collected as part of this study will be handled in a manner compliant with the intent and letter of the regulatory processes at each of the site. Data will be collected locally at each of the sites and initial analysis will take place at each site. No PHI or PII will be shared. Only coded data will be shared across sites. The investigators agree to adhere to any and all local policy guidelines for data sharing.

1. **Information Security and Data Storage/Movement**

Non-sensitive electronic data labeled with the study assigned codes and all 18 HIPAA identifiers removed (coded data), may be stored on password protected equipment (computers/laptops/hard drives) but will not be encrypted.

To minimize the risk of the loss of confidentiality and provide for data security, conservative data management procedures have been established at all study locations involved in this project. To facilitate successful completion of the Specific Aims, identifiable data will be shared only internally. Chart reviews of coded data will be completed locally and only coded human subjects data will be shared among the sites via file transfer software, email, and/or other electronic media (CD/DVD/USB drive). Throughout the course of the study, we may place a copy of all coded data in publicly accessible online data repositories. Additionally, we intend to make our datasets publicly available at the conclusion of the study in publications and presentations. We will also share our mechanical testing (non-human subjects) results with Humotech, the emulator vendor so they can program the system. Therefore, there are no anticipated concerns with Humotech (or others) incorporating this data as part of repository. To protect privacy and prevent breaches of confidentiality, all study procedures starting with recruitment and extending through to findings dissemination will adhere to all site and IRB policies and applicable regulations. All study staff realize the importance of keeping private personal information secure and are trained biennially at the sites to minimize this risk. All study personnel will demonstrate knowledge of these regulations by completing courses of instruction through the CITI program and local HIPAA compliance offices.

Any consented photography or video will protect participants’ identity (e.g., by obscuring the subject’s face and any identifying marks like tattoos). The videos and photos may include the participant’s entire body, but they will be anonymized during data processing; the participant’s face will be blurred, any identifying marks will be covered or blurred, and then the original file will be deleted. If a participant’s voice is accidently recorded, that section of video would be altered prior to any use outside of the study team. The video camera and the recording media (e.g., SD cards, optical disks) will be stored in a locked office at the site. Photos and videos that do not contain identifiable information may also be stored on password-protected computers for future use in scientific presentations and publications.

Participant data will be collected at each site will be entered into independent and secure database. Only coded information will be entered, if necessary. In general, electronic data will be coded with links stored separately, stored on password protected drives, servers will be backed up regularly, firewalls in place, and access permitted only by study team members listed on the approved IRB protocol. All physical records pertaining to a participant’s involvement in this research study will be stored in a locked room within a locked filing cabinet. A participant number will indicate the participant’s identity on these records. A master sheet linking participant names and their participant numbers will be kept secure on a password protected computer by the principal investigator. Informed consent documents will be stored separately along with other identifiable information (such as medical records necessary to have in paper form, which will be limited). Consent documents and HIPAA authorizations will be kept for a minimum of 6 years following study closure. Paper files will be stored in a locked facility to which only study investigators and study team members will have access. Because this is a multi-site study, extra care will be taken not to share protected health information or other identifiable information about participants across sites. Upon completion of the research project, in accordance with local policy, we will ensure that study data be removed from all servers, desktops, removable storage devices, etc. Hard copy data with identifiable and/or sensitive information will be shredded. Electronic data containing identifiable information will be wiped using approved software.

Access to the data for processing and participant tracking will be limited to members of the research team. Coded data files may be sent off-site via DoD Safe or encrypted email to our biostatistician, off-site collaborators, between study investigators, and to the public according to established local data transmission guidelines and in accordance with procedures monitored by the IRB and the local Research and Development and Privacy Officer. Although every effort will be made to conduct study procedures in private, some subject interactions may, in a manner consistent with standard clinical assessment, take place in a common area, like a clinical treatment space where other patients may be receiving care. The study team will use standard practices to preserve the privacy of the participant as much as possible, such as refraining from discussing sensitive topics, discussing being in a research study, referring to private health information or other personally identifiable information.

All participant information will be handled in a confidential manner consistent with HIPAA policies. However, in unusual cases, the research records may be inspected by appropriate government agencies or be released in response to an order from a court of law. The investigators acknowledge that representatives of HJF and USAMRMC will also be eligible to review study records. Identifiable protected health information such as name, patient identifying number (required to identify an individual’s medical records), and contact information will be secured in a password protected electronic database at each site. This database will also contain the participant’s de- identified alpha-numeric code. As part of the data transfer plan, data will be shared between sites using a secure and approved platform such as encrypted email or the DoD SAFE web application. This encrypted Military file transfer system allows only designated recipients to download files. If SAFE becomes unusable at any point in time during the study, the investigative team will use the DoD’s or VA’s designated replacement program. Demographic and injury related identifiable information will be maintained and stored in a secure place according to institutional regulatory guidelines.

There are no plans to share data with providers outside the study team. The Principal Investigator and other members of the immediate study team (Research Coordinator, Research Assistant) will have access to study records and data. Beyond this, study results will be shared with the scientific community. The results of this study may be used for teaching, research, publications, or presentations at scientific meetings. When the results of this research are published or discussed in conferences, no information will be included that would reveal a subject’s identity. If a subject’s individual results are discussed, their identity will be protected by using a unique subject identifier rather than their name or other identifying information. Examples of identifying information may include medical record number, Social Security number, or address. The results of this study may be published, but subject records will not be revealed unless required by law.

